### Laboratory procedures

**
*Microscopy for asexual and gametocyte quantification.*
** Thick and thin blood films will be taken from eligible expectant women participants. The thin blood films will be fixed with 100% methanol and stained with 3% Giemsa stain for 45 minutes before being examined for parasites. Thick films will be air-dried before staining. Two independent readers will determine the malaria parasite and gametocyte presence or absence; a third reader will resolve discordant readings.

**
*RNA extraction.*
** 200 µL of whole blood from each study participant will be stored (1:5) in 1000 µL RNA Protect Cell Reagent (Qiagen, Australia) at −80 °C until RNA extraction. RNA extraction will be performed on the whole sample using RNeasy Plus Mini Kit (Qiagen, Australia) following the manufacturer's instructions with the treatment of DNase on-column digestion using RNase-Free DNase set (Qiagen, Australia) to eliminate genomic DNA. 100 µL of RNA extract will be eluted.

**
*qPCR quantification of gametocyte carriage.*
** qPCR will be performed using an in-house protocol. Sex-specific qRT-PCR assays will measure RNA transcripts specific to female and male gametocytes. For example, we will target the
*Plasmodium falciparum* gametocyte surface protein (pfs25) mRNA as the female marker and the
*P. falciparum* PF3D7_1469900 mRNA transcript a recently characterized gametocyte-enriched transcript (
*Pf*MGET) as the male marker,
Table 2 below lists our expanded panel of primer probes. All qRT-PCR assays will be conducted with a One-Step RT-PCR mix (Qiagen, Australia) using methods previously described (
Collins *et al.*, 2018) with optimization and validation using cultures P. falciparum gametocytes. Our in-house controls ensure specificity and sensitivity for detecting gametocyte markers. Briefly, 0.45 µM of each primer and 0.18 µM of Taqman probe will be used in each PCR reaction. Amplification will be performed in Applied Biosystems QuantStudio [model number QuantStudio TM 5-96 well 0.2ML Block) Real-Time PCR System under the following cycling conditions: 50 °C reverse transcription for 30 min, 95 °C incubation for 15 min, followed by 45 cycles of 95 °C for 15 s and 60 °C for 60 s. Internal control available in-house will be used to quantify the gametocyte carriage.

**Table 2. T2:** Expanded primer probe panel for the qPCR assay.

Target	Gene	Primer/Probe Sequences
**AP2-G** (commitment)	PF3D7_1222600	F: GGAAAGATACGACAAGAGGACAT R: CCATTCTCAATGCACCATCATTAC Probe: FAM-CCCTGTATACCCTTCTTCGAAAGCATGC-MGB
**SBP1** (both male and female)	PF3D7_0501300	F: CCGACGAACCAACACAATTAC R: ACTAGCTGCTTCTCCAACTAAA Probe: JOE-TTGGCCGAAGTAGTTTCGGATGCA-MGB
**GEXP5** (female)	PF3D7_0936600	F: AGTGCTGAGGATAAGGATTCATT R: CACCACTTCTCAAACAACCACT Probe: Texas Red-AGCTGTCTGAATTAGTAGACTCCA-MGB
**CCP4** (novel female)	PF3D7_0903800	F: CACATGAATATGAGAATAAAATTG R: TAGGCGAACATGTGGAAAG Probe: FAM-AGCAACAACGGTATGTGCCT-MGB
**P25** (female)	PF3D7_1031000	F: TAATGCGAAAGTTACCGTGGA R: ACAGTCTTTTCGTCACATTTCAG Probe: JOE-TCAGATGAGTGGTCATTTGGA-MGB
**PfMGET** (male)	PF3D7_1469900	F: CGGTCCAAATATAAAATCCTG R: TGATTCATTTTCTTGCTTCAGA Probe: VIC-CAGCTCCAGCATTAAAAACACA-MGB

**
*DNA extraction and SP resistance testing.*
** Resistance to SP has been linked to point mutations in the parasite dihydrofolate reductase (
*dhfr*) and dihydropteroate synthase (
*dhps*) genes, which we will analyse. The
*dhfr* mutation confers resistance to pyrimethamine (
Lozovsky *et al.*, 2009), while
*dhps* confer resistance to sulfadoxine and other sulpha drugs. Parasite genomic DNA will be extracted from EDTA blood samples using commercially available DNA Qiagen kits,
*dhfr* and dhps fragments will be amplified using in-house nested PCR sequence protocols. Nested purified PCR products will be sequenced using a Big Dye Terminator v3.1 cycle sequencing kit. The reactions will be precipitated in 70 % ethanol to clean up dye terminators, rehydrated in 10 ul HiDi formamide and then sequenced on a 3130 ABI Genetic Analyzer.
Table 1 indicates a summary of laboratory procedures.

### Ethics statement

 Approval for the study was obtained from the Kenya Medical Research Institute (KEMRI) Scientific Ethics Review Unit (SERU) with the reference number KEMRI/SERU/5071 on November 14, 2024. A research license from the National Commission for Science, Technology, and Innovation was granted on December 6, 2024, under (Ref No. 503343). Additionally, the Kilifi County Department of Health Services approved the study to be conducted in Kilifi County on December 16, 2024. We will seek written informed consent from expectant mothers who are eligible to participate in this study.

### Data storage

Data will be collected in the field using electronic handheld devices. All data will be backed up daily on a remote server within the Kilifi site and the secondary server in Nairobi.

### Data management

Data collected for this study will be part of the larger dataset at the CGMR-C, which links clinical, laboratory, and demographic databases and is written in MySQL software
https://www.mysql.com, an open source database. This system is managed centrally, and this study will use existing data managers who will assist in conducting data checks and providing datasets when needed by the study investigators.

### Statistical analysis

Participant socio-demographic characteristics will be summarised by numbers and percentages if categorical. Continuous data will be summarised by mean, standard deviation (SD), and range if data are normally distributed and median, interquartile range (IQR) and range if data are skewed. We will summarise the prevalence of
*Plasmodium falciparum* infections and Pf gametocyte carriage in pregnant women, together with the associated 95% Agresti-Coull confidence interval. The Chi-square test will compare prevalence across groups (such as size and other characteristics). Regression analysis will be used to investigate factors affecting the uptake of three or more doses of IPTp-SP in Kilifi. Data will be analysed in version 17.0 (Stata Corp, College Station, TX), and graphs will be generated using R (
R Core Team, 2024). Furthermore, we will describe the relationship between IPTp-SP doses and the frequency of SP-resistant parasites.

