### Sample size

The minimum required base sample size using individual randomization (
Daniel, 1999):

$$n\geq \frac{Z_{\alpha /2}^{2}P(1-P)}{d^{2}}Deff$$

With P being the expected prevalence of malaria in the study area (in proportion to one) and d the required level of precision taken to be half of P here. Assuming a 7.1% malaria prevalence based on a previous study on malaria prevalence among adults aged 15–49 years in Kilifi (
Kamau *et al.*, 2020), we get a sample of size
*n* = 202 pregnant women, which after increasing by a design effect factor of 2 and 15% to take care of contingencies gives 475.

*Sample distribution across the study sites*

Kilifi County exhibits heterogenous malaria transmission 

Low transmission: Ngerenya (North) and Kilifi townModerate transmission: Pingilikani and Junju (South) (
Kimenyi *et al.*, 2022;
Mogeni *et al.*, 2016).

Given that gametocyte carriage varies with transmission intensity, age and recent malaria episodes and SP use (
Jafari-Guemouri *et al.*, 2018;
Muthui *et al.*, 2019; Stepniewska
*et al.*, 2008) and IPTp-SP use is uniform across the county, we will recruit proportionally from all sites (Pingilikani, Junju, Ngerenya, and Kilifi County hospital) until the target sample size (n = 475) is reached.

To understand the factors affecting the uptake of three or more doses of IPTp-SP in Kilifi, we will analyze surveillance data from the Kilifi Perinatal and Maternal (KIPMAT) study (
Seale *et al.*, 2015). The KIPMAT study was established at the Kilifi County Hospital in 2011 to standardize admission procedures to improve the clinical care for expectant women (
Seale *et al.*, 2015). It was a clinical surveillance study of pregnant women and their newborns. The study was embedded into the routine clinical care as a way of supporting and improving clinical care in resource limited setting. At admission for labour, all mothers were registered by trained fieldworkers. Data were collected on residential location, age, education level, gravidity, HIV status, ANC visits and SP frequency. At delivery, fieldworkers recorded information on delivery outcomes, sex, gestational age and infant weight. Data were saved onto the My Structured Query Language (MySQL) database.

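### The sample size carries an unexplained design effect of 2, but the planned intervals and tests treat all women as independent draws from one population

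*Protocol article*

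**What the plan says.** The Sample size section starts from a single-proportion precision formula, described as "The minimum required base sample size using individual randomization". Its inputs are an expected prevalence of 7.1% and a half-width of half that prevalence. The result is "202 pregnant women, which after increasing by a design effect factor of 2 and 15% to take care of contingencies gives 475". No cluster unit, intra-cluster correlation or source is given for the factor of 2.

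The same section then turns to the distribution of the sample over the sites. It says that "Kilifi County exhibits heterogenous malaria transmission", classes Ngerenya and Kilifi town as low and Pingilikani and Junju as moderate transmission, notes that gametocyte carriage varies with transmission intensity, and plans proportional recruitment over the four facilities. It does not say to what the recruitment is proportional.

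The Statistical analysis section summarises the prevalence of infection and of gametocyte carriage "together with the associated 95% Agresti-Coull confidence interval". For comparisons, "The Chi-square test will compare prevalence across groups (such as size and other characteristics"). It attaches no facility term, weight, stratification or effective sample size to either method. It names regression only for the uptake of three or more SP doses, which the Sample size section assigns to the separate KIPMAT data.

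**The concern.** A design effect of 2 means that the variance of the estimated prevalence is taken to be twice that of a simple random sample of the same size. The usual Agresti-Coull interval and the Pearson chi-square test both use the simple-random-sample variance. The plan therefore recruits for one variance and analyses with another.

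At stake is the stated precision of the estimates for specific objectives 1 and 2, which are prevalences with their intervals. Also at stake is the reading of group comparisons, above all SP dose against gametocyte carriage. The plan itself names transmission intensity as a determinant of carriage. A pooled comparison has no protection if dose and facility turn out to be related.

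**Working it through.** **Inputs (Sample size and Statistical analysis sections).** P = 0.071; d = P/2 = 0.0355; two-sided 95%, z = 1.96; design effect (Deff) 2; contingency 15%; final N = 475; four facilities.

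**The plan's own figure.**
- Base: 1.96² × 0.071 × 0.929 / 0.0355² = 201.05, rounded up to 202.
- Design effect: 202 × 2 = 404.
- Contingency: 404 / 0.85 = 475.3, which matches 475.
- With the doubled variance, 404 women give a half-width of 1.96 × √(2 × 0.071 × 0.929 / 404) = 3.54 points, which is the intended d. The target precision therefore already includes the factor of 2.

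**Interval at about 7.1% of 475 (34 positives).** Agresti-Coull uses ñ = n + z², p̃ = (x + z²/2)/ñ and half-width z√(p̃(1 − p̃)/ñ).

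| | x | n | p̃ | Half-width | Interval |
|---|---|---|---|---|---|
| As planned | 34 | 475 | 0.0750 | 2.36 points | 5.1% to 9.9% |
| Effective n = n/2 | 17 | 237 | 0.0786 | 3.40 points | 4.5% to 11.3% |

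The ratio of half-widths is 3.40/2.36 = 1.44, close to √2. With 404 women, the number before contingency, the half-widths at 7.1% are 2.56 points as planned and 3.69 points on n/2, the same ratio.

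**Coverage if Deff = 2.** 2Φ(1.96/√2) − 1 = 2Φ(1.386) − 1 = 0.834. A beta-binomial simulation (four sites, Deff 2, 100,000 runs) gave 84% for the planned interval and 96% for the interval on n/2.

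**Chi-square size, 1 df, nominal 5%.** For a characteristic that carries the full design effect: P(χ²₁ > 3.841/2) = 0.166. Simulation gave 16.2% for a characteristic fixed by site (two sites against two) and 4.8% for a characteristic balanced within sites.

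**Sensitivity.** The documents give no basis for the value 2, so a range is shown.

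| Deff | Coverage of nominal 95% interval | 1-df size, characteristic follows site |
|---|---|---|
| 1.25 | 92% | 8% |
| 1.5 | 89% | 11% |
| 2 | 83% | 17% |
| 3 | 74% | 26% |

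**The other reading.** If the four facilities are fixed strata and each contributes in proportion to its population, differences between sites add nothing to the sampling variance of the pooled prevalence for those sites. The simple interval is then not too narrow. But nothing in the text then explains why 202 became 404.

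**The case against.** The strongest reply is that the undercoverage is conditional. The protocol never says that the factor of 2 stands for clustering by facility. The passage on heterogeneous transmission comes later and supports proportional recruitment, not the doubling. With fixed strata, the unexplained factor merely makes the sample generous and leaves the interval sound. This stands, and it is why the point is a conflict between sections and not a proven error in the interval. It does not remove the point, because neither reading fits both sections as written.

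A reader might go further and infer that all the planned tests are too liberal. The documents do not support this. Inflation arises only for characteristics that follow facility. The plan describes SP use as uniform across the county, so the dose comparison may see little or none. Nor can an inflated size be claimed for a test among the four sites: there the site difference is the quantity being tested. A reader might also infer that the pooled prevalence depends on however many women each clinic happens to supply. The plan says recruitment is proportional; what it lacks is the basis of the proportion.

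It can also be said that a condensed article leaves variance estimation to a fuller document, and that naming Agresti-Coull does not exclude an effective sample size. The second part is true, and the fix makes use of it. But the article does state both a design effect and specific methods whose standard form ignores it, so more than missing detail is involved.

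**Conclusion.** The point holds as an inconsistency between the sample size and the analysis. If Deff = 2 is real, the planned interval for overall prevalence is too narrow by a factor of about 1.4 and covers about 83%, and 1-df tests of characteristics that follow facility have a size of up to about 17%. These figures assume that the full factor of 2 applies to the quantity analysed. They are smaller for a smaller design effect, and the size is near 5% for characteristics balanced within facilities. If the facilities are fixed strata sampled proportionally, the pooled interval is adequate for those four sites and the doubling is unsupported. The document does not allow a choice between the two readings. The change should be made before analysis and needs no new data.

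**What to change.** State what the design effect of 2 represents and where it comes from, then make the analysis match in one of two ways.

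1. **Fixed strata.** Treat the four facilities as strata, limit inference to them, and state the basis of the proportional allocation. Stratify or adjust the dose-carriage and other group comparisons by facility, with Cochran-Mantel-Haenszel or with logistic regression on facility or low/moderate transmission indicators. Use exact or penalised methods where data are sparse. The factor of 2 then needs its own justification or should be dropped from the rationale.
2. **County-wide prevalence.** If such a figure is claimed, compute its Agresti-Coull interval on n divided by the design effect, as the sample size implies.

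A cluster-robust variance is not a good substitute, because four facilities are too few to estimate it reliably.

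**Cost.** Only the analysis text changes. A county-wide interval becomes about 1.4 times wider and rests on a planning value of Deff, not an estimated one. Facility-level estimates will be sparse: 0.071 × 475 ≈ 34 positives, or 34/4 = 8.5 per facility on average, and probably fewer at the low-transmission sites.

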### Ethical considerations

We will conduct our study according to the ethical considerations outlined in the Helsinki Declaration.

**
*Risk to participants.*
** The risks to participating subjects will be those associated with fresh blood collection, including temporary local pain and possibly mild bruising. We will minimize risks to study participants by using well-trained staff to obtain blood collection from study participants. No additional blood collection will be required from those found to be RDT-negative. Participants will be approached and requested to participate in our study at the reception as they wait to be seen by the attending nurse. A request to collect an initial 0.05ml will only be made if the attending clinician has not requested an RDT malaria test. An additional blood collection of 0.35ml will be requested if the expectant woman has RDT-positive test results. We will ask for these samples (0.05ml for RDT and an additional 0.35ml if RDT positive) after the mother has completed her routine checks with the attending nurse. In addition, participation in the study will be voluntary, and participants will not incur extra costs for participating as they will be selected from routine ANC attendance. We anticipate study participants taking approximately one hour in our study procedures. We will offer refreshments to all the mothers who participate in our study.

**
*Benefits to study subjects/community.*
** There are no direct benefits to those involved in this study. It is hoped that this research will result in new knowledge that will lead to the development of alternative approaches to the prevention and treatment of malaria during pregnancy and that will be of broader benefit to all societies affected by the disease. For women with RDT-positive tests, this information will be shared immediately with the attending nurse/clinician to guide their care and management.

**
*Informed consent.*
** We will obtain written informed consent from eligible study participants. Participants will be approached and requested to participate in the study at the reception area as they wait to see the attending nurse. We will distinguish standard routine procedure from the additional consent sought for this study. We will explain that should the expectant women decline to participate in our study, the availability of health care in the dispensary or hospital will remain the same. They will be explained that they are free to decline to participate in the study should they change their mind mid-way into consenting to the study or at any point during the study procedures.

For those who consent to participate in our study, after they complete their routine checks, and if the clinician has not requested a malaria test, we will request an RDT test. An additional blood sample will be ordered from those with malaria parasites. This will involve the inconvenience of a further blood sample. We will use trained fieldworkers for consenting. All malaria episodes will be managed per standard practice at the designated dispensary or hospital.

**
*Community engagement.*
** A CAST (Community Engagement Advice for Studies) group will be set up to support the planning and implementation of engagement activities. CASTs are study-specific groups set up by the Community Liaison Manager in CGMRC and includes members of the Community Liaison Group and core members of the study team. The CAST group will advise throughout the study on community engagement, including strategic planning and responding to any emerging issues during the study. The CAST group will also be able to support similar activities at the participating health facilities.

We will seek to engage the Sub-County Health Managers for the four participating health facilities (Ngerenya, Junju, Pingilikani and KCTRH) at the onset of the study. Before beginning the study, we will also contact the hospital and dispensary committee, the staff at ANC, and other community leaders within the targeted facilities. We will provide regular updates when required. Furthermore, at the end of the study, we will communicate and share the study results with participants and communities at all the study sites. Results will be shared at a population level, not per everyone's outcome.

We are aware (from our previous community engagement activities) that studies among pregnant women can be sensitive, especially where blood is drawn -and for our case, more than once if RDT is positive)- as such, key messages will be carefully developed to address any community concerns during the engagement. Our fieldworkers will also work with the healthcare workers to participate in the routine health talks. The fieldworkers will use the health talk platform to mention our study activities in the participating health facilities.

**
*Methods for maintaining confidentiality.*
** Data will be stored on password-protected servers in the KEMRI-CGMRC. Datasets shared with collaborators for analysis will be de-identified, i.e. not include participants' names but rather a study number).

**
*Data sharing and protection.*
** In the future, de-identified information collected or generated during this study may be used to support new research by other researchers in Kenya and other countries interested in understanding malaria in pregnancy. In all cases, we will only share information with other researchers in ways that do not reveal individual participants' identities following appropriate permissions. Any future research using information from this study must first be approved by a local (including the data governance committee) or national ethics committee.

The data from this study will undergo strict quality control before it is released for local analysis or external sharing. The cleaned data will be made available to study investigators. Priority will be given to access to the data analysis and publication to the study investigators before the data can be made publicly available. Study participants will have appropriately been informed about safeguarding confidentiality should their data be shared with external researchers after the study—requests for data from external investigators after publication can be made through the PI. If permission to use data is granted, the use will be compatible with the informed consent forms used to collect the data. The study site will keep personally identifiable information about participants from this study for seven years after the study has finished under applicable Data Protection Requirements in Kenya. Study participants have the right to access the personal data we hold that pertains to them and to object to or make corrections to the processing of all or part of the personal data.

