*et al.* study analysed samples from young children; therefore, it is unknown whether SP mutant parasites are also on the increase in pregnant women who continue receiving SP and that warranty investigation. There are conflicting data on the risks and benefits of IPTp-SP. Previous studies indicate that even if there is a rise in the prevalence of molecular markers of resistance among pregnant women, SP can effectively reduce the malaria burden during pregnancy and extend protection to non-malarial cases of low birthweight (
Taylor *et al.*, 2012). However, the SP, used for curative or preventive treatment, is associated with microscopic and sub-microscopic gametocytaemia, contributing to sustained malaria transmission (
Bousema & Drakeley, 2011). Furthermore, SP provides intermittent clearance or suppression of existing asymptomatic infections from the placenta and can prevent new infections for several weeks by maintaining suppressive drug levels (
Karunajeewa *et al.*, 2009). It is this prolonged clearance period for SP that drives gametogenesis.

Our study aims to understand the dynamic of gametocyte carriage in pregnant women under intermittent preventive treatment with sulfadoxine-pyrimethamine, specifically if the varying doses of SP influence gametocyte carriage. We will also assess SP resistance markers in women under IPTp-SP. To comprehensively understand the determinants of IPTp-SP uptake, we will utilize a dataset from a previous study, the Kilifi Perinatal and Maternal (KIPMAT) study. Previously, the data was used to assess the impact of IPTp-SP on birth outcomes (
Kamau *et al.*, 2023). In the present study, we will apply the logistic regression model to evaluate predictors of uptake of optimal doses of IPTp-SP.

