### Sampling and recruitment procedures

Women who meet our study inclusion criteria and reside within the Kilifi Health Demographic and Surveillance Site will be recruited for our study. We will recruit participants from four health facilities: KCTRH, Ngerenya, Pingilikani and Junju. We will recruit expectant women during routine ANC visits at the four health facilities. We will approach and consent eligible participants after the attending nurse or clinician has seen them. The KEMRI CGMRC has had a long-standing engagement with these health facilities. As part of the study engagement activities prior to study imitation, we will request that the health facility allocate us a small room or space to set up a temporary room so we can confidentially consent our study participants and for other study-related activities. Since one of our eligibility criteria is that the expectant women should have had at least one dose of SP and the current guidelines state that "provision of SP should be done for above 13 weeks' of gestation", we anticipate recruiting women who will be attending their second or more ANC visits when standard antenatal care profile procedures (blood group, HB measurements, malaria test, blood glucose, syphilis, and urine protein etc) will have already been done. We cannot use this routine blood from the antenatal care profile procedures. However, if the participant is required to undergo an RDT malaria test as part of their routine care, we will only request an additional 0.35ml, collected using a fingerpick, from them if they turn RDT positive. We will collect blood for the RDT and the additional 0.35ml (if malaria-positive) only after the participant completes routine checks with the attending nurse. We anticipate that study participants will take approximately 1 hour to participate in our study procedures. Blood samples from study participants will undergo tests listed in
Table 1 below. We will collect the following demographic data from eligible study participants: mother's age, marital status, education level, parity status (based on parity and gravida), number of ANC attendance and number of doses of malaria prophylaxis.

**Table 1. T1:** Sample collection and laboratory procedures.

Goal	Laboratory procedures	Location	Volume of blood required
Rapid malaria detection	RDT	To be done at the ANC clinic	50ul

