Presence or absence of malaria parasites	Microscopy (gold standard)	Additional blood samples will be shipped to KEMRI- CGMRC laboratories	50ul
Gametocyte carriage	qPCR		200ul
Detection of resistance to SP markers	DNA extraction, Sanger/NGS sequencing		100ul
Total blood volume			400 ul (0.4ml)

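### The protocol both restricts the gametocyte and microscopy sample to RDT-positive women and takes it from every participant; under the restriction, gametocyte prevalence in pregnant women is not estimable

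*Protocol article*

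**What the plan says.** **Who gives the extra sample.** Sampling and recruitment procedures says, of women having an RDT in routine care, that "we will only request an additional 0.35ml, collected using a fingerpick, from them if they turn RDT positive". Ethical considerations (Risk to participants) extends the rule to women whose RDT is added by the study: "An additional blood collection of 0.35ml will be requested if the expectant woman has RDT-positive test results", and "No additional blood collection will be required from those found to be RDT-negative". The Informed consent paragraph agrees: "An additional blood sample will be ordered from those with malaria parasites".

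**What the sample is for.** Table 1 lists 50 µL for the RDT, 50 µL for microscopy (labelled the gold standard), 200 µL for gametocyte qPCR and 100 µL for SP resistance markers, 400 µL in total.

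**The conflicting text.** Laboratory procedures (RNA extraction) says that 200 µL "of whole blood from each study participant will be stored". The microscopy paragraph there takes thick and thin films from eligible participants. Neither mentions the RDT result.

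**What is promised.** Specific objectives 1 and 2 are the prevalence of *P. falciparum* infection and of gametocyte carriage in pregnant women, the latter with its association with IPTp-SP doses. Statistical analysis plans both prevalences with 95% Agresti-Coull intervals. The Introduction gives as motivation that SP "is associated with microscopic and sub-microscopic gametocytaemia, contributing to sustained malaria transmission".

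**The concern.** Field staff cannot follow both rules, and the rule chosen decides what the study estimates. Under the RDT rule, a woman with a negative RDT has no gametocyte result by any method, so the data for objective 2 do not cover the population it names. Microscopy cannot find an infection that the RDT missed, although Table 1 makes it the reference test for the presence of parasites.

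The dose question is affected as well. The Rationale says that SP clears existing asymptomatic infections, so the number of doses may influence whether a woman is RDT-positive at her visit. A comparison of gametocyte carriage by dose among RDT-positive women is then made within a group that dose may have helped to select. The Study limitations paragraph treats low parasitaemia only as a problem of assay yield in collected samples. It does not say that RDT-negative women give no sample. Blood not taken at the visit cannot be recovered later.

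**Working it through.** **1. The plan's own sample size.** Inputs from Sample size: P = 0.071, d = P/2 = 0.0355, design effect 2, contingency 15%. The formula shows no value for Z; 1.96 is assumed, in line with the 95% intervals.

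- n = 1.96² × 0.071 × 0.929 / 0.0355² = 201.05, rounded up to 202 (stated: 202).
- 202 × 2 = 404; 404 / 0.85 = 475.3 (stated: 475).

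The figure reproduces. It is sized for malaria prevalence in all enrolled women.

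**2. What the 0.35 ml contains.** Microscopy 50 + qPCR 200 + resistance markers 100 = 350 µL = 0.35 ml. Adding the 50 µL for the RDT gives the Table 1 total of 400 µL. The RDT-dependent sample is therefore all the blood for these three tests. Only the RDT is done in everyone.

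**3. Women with a result under the RDT rule**, taking the planned 7.1% as the RDT-positive proportion:

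| N | RDT-positive | No result beyond the RDT |
|---|---|---|
| 475 | 475 × 0.071 = 33.7 | 441.3 (93%) |
| 462 (abstract) | 32.8 | 429.2 |
| 404 (before contingency) | 28.7 | 375.3 |

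Across the planned precision of 7.1% ± 3.55 points, the number at N = 475 runs from 475 × 0.0355 = 16.9 to 475 × 0.1065 = 50.6.

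**4. What can be estimated.**

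- *RDT-defined infection prevalence:* yes, in all women. 34/475 = 7.2%, 95% Agresti-Coull interval 5.1% to 9.9%, before any design effect.
- *Gametocyte carriage among RDT-positive women:* yes, but imprecisely. For illustration, assume 10 of 34 are positive: 29%, interval 17% to 46%.
- *Gametocyte carriage in all enrolled women:* no. With the same 10 positives the data give only a floor of 10/475 = 2.1%. With 441 women untested, the ceiling is (10 + 441)/475 = 95%.

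**5. How far the floor could lie from the truth.** No document gives the carriage in RDT-negative women, so an assumed range is shown, with true prevalence = (10 + 441q)/475:

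| Assumed carriage q in RDT-negatives | True prevalence | Share of carriers found |
|---|---|---|
| 1% | 3.0% | 69% |
| 2% | 4.0% | 53% |
| 5% | 6.7% | 31% |
| 10% | 11.4% | 18% |

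The table shows only that the answer depends on a quantity the RDT rule leaves unmeasured.

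**The case against.** **The rule has a reason.** Ethical considerations presents limited blood-taking as a way to keep the burden on pregnant women low. That is a legitimate choice. It does not remove the contradiction with Laboratory procedures or the mismatch with objective 2.

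**The bias follows only under one reading.** If the Laboratory procedures text is the intended one, every woman has a gametocyte result. This is correct, and the certain defect is the contradiction. However, two sections and the Table 1 volumes favour the RDT rule.

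A reader might also infer more than the document supports:

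- *That P. falciparum prevalence cannot be estimated at all.* Every consenting woman has an RDT, and the objectives name no diagnostic method. Only prevalence by microscopy, or by a test more sensitive than the RDT, is lost.
- *That low-density carriage is never looked for.* qPCR can find sub-microscopic gametocytes in RDT-positive women. It is in RDT-negative women that none are sought.
- *That limiting sequencing to RDT-positive women is a fault.* Resistance markers can be read only where parasite DNA is present, so this restriction is not in itself an error.
- *That recorded infection prevalence will be too low by a calculable amount.* Multiplying 7.1% by an assumed RDT sensitivity treats 7.1% as true prevalence, and the protocol does not say how it was measured. It also assumes perfect specificity. With an assumed 70% sensitivity and 97% specificity, the RDT would read 0.071 × 0.70 + 0.929 × 0.03 = 7.8%, above 7.1%.
- *That SP-cleared women who still carry gametocytes are known to be the ones left out.* The Introduction reports resistant parasites that SP fails to clear, with the quintuple mutant at 83.6% in Kilifi in 2018 (in children). How many such women exist is unknown.

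**Conclusion.** The point stands. The sampling rules contradict each other and must be reconciled. If the RDT rule governs, about 34 of 475 women have a microscopy or gametocyte result and about 441 have none. Gametocyte prevalence in pregnant women, as promised in Specific objectives and Statistical analysis, is then not estimable, and only a lower bound is available over all enrolled women. Infection prevalence is estimable as RDT-defined prevalence and not by the protocol's own reference test. The dose comparison rests on about 34 women selected on a variable that dose may affect; the size and direction of any resulting bias are unknown.

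The count of 34 assumes that the planned 7.1% equals the RDT-positive proportion. The conclusion about what can be estimated does not depend on that figure.

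**What to change.** Reconcile Laboratory procedures with Sampling and recruitment procedures and Ethical considerations, so that one rule states who gives the 0.35 ml.

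**If the RDT rule stays:**

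- define objective 1 as RDT-detected prevalence, with microscopy as confirmation in RDT-positive women;
- define objective 2 as gametocyte carriage, and its association with SP dose, among RDT-positive women;
- report gametocyte-positives over all enrolled women only as a labelled lower bound;
- align the wording of Laboratory procedures and Statistical analysis;
- add the selection on RDT positivity to Study limitations, noting that SP dose may influence it.

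This costs wording only. The price is a narrower claim for objective 2, resting on few women.

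**If sampling every participant is intended:** correct Sampling and recruitment procedures and Ethical considerations to say so. Objective 2 can then stand as written. The cost is about 441 further small samples with their assays, and an ethics and consent amendment.

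A random 1-in-5 sample of RDT-negative women (441/5, about 88) is a weak compromise. At an assumed carriage of 1% or 2%, the chance of finding no carrier is 0.99^88 = 41% or 0.98^88 = 17%, and each carrier found would count as five.
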